#### Formula of Pooled Standard Deviation:

$$Pooled\ SD = \sqrt{\frac{(n_1 - 1) \times SD_1^2 + (n_2 - 1) \times SD_2^2}{n_1 + n_2 - 2}}$$

Pooled standard deviation

$$= \sqrt{[(150-1) \times 19.0^2 + (1137-1) \times 12.3^2] / (150+1137-2)}$$

$$= 13.251663$$

#### Sample size estimated using G-power calculator:

**F tests** - ANOVA: Repeated measures, between factors

**Analysis:** A priori: Compute required sample size

|                |                           |              |
|----------------|---------------------------|--------------|
| Input:  | Effect size f             | = 0.3244754  |
|                | α err prob                | = 0.05       |
|                | Power (1-β err prob)      | = 0.80       |
|                | Number of groups          | = 2          |
|                | Number of measurements    | = 4          |
|                | Corr among rep measures   | = 0.5        |
| Output: | Noncentrality parameter λ | = 8.4227428  |
|                | Critical F                | = 4.0426521  |
|                | Numerator df              | = 1.0000000  |
|                | Denominator df            | = 48.0000000 |
|                | Total sample size         | = 50         |
|                | Actual power              | = 0.8115763  |

Therefore, a sample size of 25 are required for each group.

While there is no reported raw data for variance or partial eta-squared that is required to generate the effect size for determining the within group mean difference in symptom control and quality of life, a rule of thumb is used to determine the magnitude of the effect size. Generally, three different effect sizes can be generated from the different levels of partial eta-squared when using the rule of thumbs. 0.01 is meant for a small treatment effect, 0.06 is for medium, and 0.14 is for large effect size (Cohen, 1988). For this study, we estimate a small effect in order to yield the highest number of samples, and hence 0.01 is selected for partial eta-squared in order to generate an effect size. The G-power sample size calculator is used by setting the probability (power) at 0.8, the Type I error probability associated with this

test of this null hypothesis at 0.05, and the function of repeated measures, an effect size of 0.1005038 within factors ANOVA analysis. The total sample size calculated is 138, with 69 samples required for each group. The sample size calculation is shown below.

#### **Sample size for within-group differences in symptom control and quality of life**

Researcher estimate a small treatment effect size by select 0.01 for Partial eta-squared and input into G-power calculator.

#### **Results of the G-power calculator:**

F tests - ANOVA: Repeated measures, within factors

Analysis: A priori: Compute required sample size

Input: Effect size  $f$  = 0.1005038

$\alpha$  err prob = 0.05

Power ( $1-\beta$  err prob) = 0.80

Number of groups = 2

Number of measurements = 4

Corr among rep measures = 0.5

Nonsphericity correction  $\epsilon$  = 1

Output: Noncentrality parameter  $\lambda$  = 11.1515193

Critical F = 2.6267747

Numerator df = 3.0000000

Denominator df = 408

Total sample size = 138

Actual power = 0.8056554

Therefore, 69 samples are required for each group

The sample size selected will be 70 participants for each group after considering the highest sample size calculated for each specific objective. By estimating the predicted drop-out rate of 10%, 77 participants for each group will be required for this phase. A total of 154 participants will be recruited for this study.

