### Secondary Objective

To determine within group difference for the 4 primary parameters (knowledge, symptom control, medication adherence, quality of life)

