## Sample size

Prior data indicate that in determining patients' knowledge level with regard to the use of intranasal steroids for AR treatment, the mean score of adults with adequate knowledge about allergic rhinitis treatment among controls is estimated to be 1.39 (SD:0.71), and the estimated true mean score of adequate knowledge for interventional subjects is 1.70 (SD: 0.58) assuming 77 participants in each group (Retinasekharan et al., 2021). By using the G-power calculator, this study will need 67 interventional participants and 67 control participants to be able to reject the null hypothesis that the mean scores of the interventional

and control groups are equal with probability (power) 0.8. The Type I error probability associated with this test of this null hypothesis is 0.05. The calculation is shown below:-

Sample size estimation for the mean difference of knowledge level between groups

Intervention group

Mean score: 1.70

Standard Deviation: 0.58

Control group

Mean score: 1.39

Standard Deviation: 0.71

Pooled standard deviation

$$\begin{aligned} \text{Pooled } SD &= \sqrt{\frac{(n_1 - 1) \times SD_1^2 + (n_2 - 1) \times SD_2^2}{n_1 + n_2 - 2}} \\ &= \sqrt{[(77-1) \times 0.71^2 + (77-1) \times 0.58^2] / (77+77-2)} \\ &= 0.648267 \end{aligned}$$

Results of the G-power calculator:

F tests - ANOVA: Repeated measures, between factors

Analysis: A priori: Compute required sample size

|                                     |             |
|-------------------------------------|-------------|
| Input: Effect size f                | = 0.2005347 |
| α err prob                          | = 0.05      |
| Power (1-β err prob)                | = 0.80      |
| Number of groups                    | = 2         |
| Number of measurements              | = 3         |
| Correlation among repeated measures | = 0.5       |
| Output: Noncentrality parameter λ   | = 8.0830473 |
| Critical F                          | = 3.9128750 |
| Numerator df                        | = 1.0000000 |
| Denominator df                      | = 132       |
| Total sample size                   | = 134       |
| Actual power                        | = 0.8057571 |

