To determine the sample size required for the mean difference of symptom control between the intervention and control group, studies using TNSS as a symptom control evaluation tool, with the study design of a randomised controlled trial, recruiting a study population of intermitent or persistent AR, and possibly in Asian countries, were searched. The information from a randomised controlled trial that investigated the change in TNSS after an intervention vs. a placebo in adults in China with intermittent or persistent AR was used to estimate the sample size (Han et al., 2011). The G-power sample size calculator is used by setting the probability (power) at 0.8, the Type I error probability associated with this test of this null hypothesis at 0.05, the effect size at 0.3850550, and the function of repeated measures,

between factors ANOVA analysis. A sample of 18 participants is required for each group.  
The calculation is shown below.

Sample size estimation for the mean difference of symptom control between groups

Intervention group

Mean score: 3.991

Standard Deviation: 2.2145

n=181; reference: (Han et al., 2011)

Control group

Mean score: 5.704

Standard Deviation: 2.2341

n=182 reference: (Han et al., 2011)

Pooled Standard Deviation:

$= \sqrt{[(181-1) \times 2.2145^2 + (182-1) \times 2.2341^2] / (181+182-2)}$

$= 2.2243$

Results of the G-power calculator:

F tests - ANOVA: Repeated measures, between factors

Analysis: A priori: Compute required sample size

Input: Effect size f = 0.3850550

α err prob = 0.05

Power (1-β err prob) = 0.80

Number of groups = 2

Number of measurements = 4

Correlation among repeated measures = 0.5

Output: Noncentrality parameter λ = 8.5401995

Critical F = 4.1300177

Numerator df = 1.0000000

Denominator df = 34.0000000

Total sample size = 36

Actual power = 0.8102902

Therefore, 18 samples are required for each group

The mean of adherence rate to intranasal corticosteroid among control is 76.62 (SD: 2.848386), while the adherence rate for the intervention group is 93.94 (SD: 2.84) (Feng et al., 2017). By using G-power calculator, we will need to study 2 intervention and control groups, respectively, to be able to reject the null hypothesis that the adherence for intervention and control participants is equal with a probability (power) of 0.8. The Type I error probability associated with the test of this null hypothesis is 0.05. The calculation is shown below:-

525 Intervention group  
 526 Mean: 93.94  

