 527 Standard Deviation: 2.84  
 528 n=16; reference: (Feng et al., 2017)  
 529  
 530 Control group  
 531 Mean score: 76.62  
 532 Standard Deviation: 2.848386  
 533 n=13; reference: (Feng et al., 2017)  
 534  
 535 Pooled Standard Deviation:

$$536 \quad Pooled\ SD = \sqrt{\frac{(n_1 - 1) \times SD_1^2 + (n_2 - 1) \times SD_2^2}{n_1 + n_2 - 2}}$$

537 Pooled standard deviation  
 538 =  $\sqrt{[(16-1) \times 2.84^2 + (13-1) \times 2.848386^2] / (16+13-2)}$   
 539 = 2.843730

541 Results of the G-power calculator:

542 **F tests - ANOVA:** Repeated measures, between factors

543 **Analysis:** A priori: Compute required sample size

544 **Input:** Effect size f = 3.0289576

545 α err prob = 0.05

546 Power (1-β err prob) = 0.80

547 Number of groups = 2

548 Number of measurements = 3

549 Corr among rep measures = 0.5

550 **Output:** Noncentrality parameter λ = 55.0475049

551 Critical F = 18.5128205

552 Numerator df = 1.0000000

553 Denominator df = 2.0000000

554 Total sample size = 4

555 Actual power = 0.9350969

556

557 A study mapping the naso-ocular symptom scores to EQ-5D-5L utility values was referred to  
 558 in order to obtain the input of mean scores and standard deviation to estimate the sample  
 559 size required to compare patients' QoL between two groups. The EQ-5D-5L utility values in  
 560 mean and standard deviation were corresponding to the disease severity in AR patients,  
 561 where the utility values of  $1.000 \pm 0.000$ ,  $0.943 \pm 0.085$ ,  $0.909 \pm 0.095$ ,  $0.849 \pm 0.142$ , and  
 562  $0.767 \pm 0.175$  were corresponding to none, mild, moderate, severe, and most severe groups  
 563 (Kumanomidou et al., 2022). In this study, patients with moderate to severe allergic rhinitis  
 564 will be recruited for control and interventional groups, and the aim of the intervention is to  
 565 improve the symptoms, if not totally absence of symptoms, at least the mild disease state.  
 566 Assuming that the control group patients would remain in the disease status of moderate to

severe and the intervention group would achieve mild disease status, the EQ-5D-5L utility values corresponding to moderate ( $0.909 \pm 0.095$ ) and mild ( $0.943 \pm 0.085$ ) were selected to simulate the mean utility score of control and intervention, respectively.

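### The 0.81 power quoted for 69 per group belongs to the time effect pooled over both arms (about 0.48 within one arm); the knowledge effect size contradicts its stated means, and the adherence spreads need checking

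*Combined protocol and SAP*

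**What the plan says.** The Secondary Objective is "To determine within group difference for the 4 primary parameters", and Table 1 defines the secondary endpoint as within-group change from Day 0 to each follow-up. The Sample size section has a calculation for within-group differences, limited to symptom control and quality of life. It enters partial eta-squared 0.01, 2 groups, 4 measurements and correlation 0.5 in a within-factors repeated measures ANOVA. The output is a total of 138, denominator df 408 and power 0.8056554, and the text concludes "Therefore, 69 samples are required for each group".

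For knowledge, the section gives means of 1.70 and 1.39 and a pooled SD of 0.648267, enters f = 0.2005347 with 3 measurements, and states that "this study will need 67 interventional participants and 67 control participants".

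For adherence, it gives means of 93.94 (n = 16, SD 2.84) and 76.62 (n = 13, "Standard Deviation: 2.848386") and concludes that "we will need to study 2 intervention and control groups, respectively".

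The final size is the largest of these results, 70 per group from EQ-5D-5L utility, raised to 77 for dropout.

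**The concern.** Because the section takes the largest size over the specific objectives, a reader will conclude that each objective has at least 80% power. For change within each arm, that conclusion rests on a test of a different quantity. The output treats 138 people as one sample for the time effect, whereas a statement about one arm rests on 69. An arm that shows no significant change could then be read as if the test had been adequately powered.

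The knowledge and adherence items raise a simpler question: whether the printed inputs are the right ones for two primary endpoints. Knowledge has means and an effect size that cannot both be correct. Adherence has spreads so small that two participants per group appear to be enough.

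**Working it through.** All powers use the noncentral F distribution at α = 0.05. N is total size, m the number of measurements, k the number of groups and ρ the correlation.

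- Within factors: λ = f²·N·m/(1 − ρ), df = m − 1 and (N − k)(m − 1), with sphericity (ε = 1) as entered in the plan.
- Between factors: λ = f²·N·m/(1 + (m − 1)ρ), df = k − 1 and N − k.
- Two groups: f = difference/(2 × pooled SD).

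**1. Within-group objective**

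The plan's figure reproduces.
- f = √(0.01/0.99) = 0.1005038.
- λ = 0.1005038² × 138 × 4/0.5 = 11.15; df 3 and (138 − 2) × 3 = 408; critical F 2.6268; power 0.8057.

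The 408 shows that the test is the time effect averaged over both arms. For one arm at the same f, k = 1:

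| n in the arm | λ | df | power |
|---|---|---|---|
| 69 | 5.58 | 3, 204 | 0.478 |
| 70 | 5.66 | 3, 207 | 0.484 |
| 77 | 6.22 | 3, 228 | 0.527 |
| 137 | 11.07 | 3, 408 | 0.802 |

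Keeping the two-group error term (df 408) and testing the time effect in one arm of 69 gives 0.482, so using the two-way model makes almost no difference. The plan does not justify ρ = 0.5. With ρ assumed at 0.3, power at n = 69 is 0.35; at 0.7 it is 0.72.

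**2. Knowledge**

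The plan's total reproduces from the f entered: f = 0.2005347, m = 3, N = 134 gives λ = 8.083, critical F 3.9129 and power 0.8058.

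That f does not come from the stated means.
- Stated difference: 1.70 − 1.39 = 0.31, so f = 0.31/(2 × 0.648267) = 0.2391.
- Difference implied by the f entered: 0.2005347 × 2 × 0.648267 = 0.2600.
- At f = 0.2391, N = 94 (47 per group) gives power 0.802, and N = 134 gives 0.92.

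**3. Adherence**

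The plan's total reproduces from the f entered: f = 3.0289576, N = 4 gives power 0.935. The stated means and pooled SD (2.843730) give f = 17.32/(2 × 2.843730) = 3.045 and power 0.937 at the same N, a trivial difference.

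The question is whether the spreads are SDs. 10.27/√13 = 2.8483855, which rounds to the printed 2.848386, and 13 is the group size printed with it. Of all n from 2 to 30, none brings 2.848386 × √n as close to a two-decimal number. The intervention value gives 2.84 × √16 = 11.36. This is compatible but is no evidence, since four times any two-decimal number has at most two decimals.

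If both values are standard errors:
- SDs are 11.36 and 10.27; pooled SD = √[(15 × 11.36² + 12 × 10.27²)/27] = 10.89.
- f = 17.32/(2 × 10.89) = 0.795.
- N = 10 gives power 0.770, N = 12 (6 per group) gives 0.859, and N = 4 gives 0.21.

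**4. Effect on the trial size**

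Utility, f = 0.1885976, m = 4, N = 140, reproduces at power 0.8004. Its 70 per group exceeds the 47 for knowledge and the 6 for adherence.

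**The case against.** The strongest reply on the within-group item is that the Statistical analysis section takes within-group findings from the two-way repeated measures ANOVA and specifies no separate test in each arm. On that reading, the within-subject time factor is what the plan powers, and 0.81 stands. It does stand for the pooled time effect. However, the objective, Table 1 and the heading of the calculation all speak of change within a group, and a time effect averaged over arms does not show change in either one.

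A second reply is that the effect was deliberately chosen small. This is fair: at partial eta-squared 0.02, one arm of 69 has power of about 0.81. The 0.48 describes the plan's own assumption and does not forecast the result.

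The knowledge error is conservative if 0.31 is right, and it does not set the trial size. Both statements are true, but the printed figures still conflict.

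Some stronger readings are tempting, and the documents do not support them.
- A reader might infer that 138 was miscalculated. It was not; it follows exactly from its inputs.
- A reader might take it as established that standard errors were used for adherence. Both values are labelled SDs and the source is not available here. From the inputs as labelled, a total of 4 does follow.
- A reader might add that "By estimating the predicted drop-out rate of 10%, 77 participants for each group will be required for this phase" should give 78, since 70/0.9 = 77.8. That is one participant per arm and immaterial.

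**Conclusion.** Two statements need correction and one needs verification.

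1. The power of 0.81 at 138 applies to the time effect pooled over both arms. For change within one arm of 69 it is about 0.48, given f = 0.1005, correlation 0.5 and sphericity. It stays below 0.80 across assumed correlations of 0.3 to 0.7. This concerns symptom control and quality of life only, the outcomes that the calculation names.
2. The knowledge means and effect size are inconsistent: 0.31 gives a total of 94, and 0.26 gives 134. The documents do not show which was intended.
3. The control spread for adherence is probably a standard error, on the strength of a match to six decimals with the printed group size. This remains an inference until the source is checked.

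The enrolment target is not undermined, because utility drives it and its calculation reproduces. Only a wish for 80% power in each arm at this small effect would raise it, to 137 per group before dropout.

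**What to change.** - **Within-group objective:** state that a total of 138 gives 0.81 for the time effect pooled over arms, and that each arm's own test has about 0.48 at 69 per group under the same assumptions.
- **Knowledge:** check the source and correct either the means or the effect size. If 0.31 is right, enter f = 0.2391 and a total of 94; if 0.26 is right, correct the means and keep 134.
- **Adherence:** check both spreads against the cited study. Only if they are standard errors, recompute with the SDs (f about 0.795, total 12).

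The cost is edits to the Sample size section and a look at two sources, with no change in enrolment. While the section is open, the EQ-5D VAS entry should be checked in the same way. Its f of 0.3244754 with pooled SD 13.251663 implies a difference of 8.6, whereas the stated means differ by 85.5 − 72.1 = 13.4, which gives f = 0.506 and a total of 22 rather than 50. This too lies below the driving figure.

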| Criteria for evaluation | Primary criteria. The differences between the intervention and control groups in the aspect of
1. knowledge of intranasal corticosteroid
2. Symptom control
3. adherence to intranasal corticosteroid administration
4. quality of life                                                                                                                                                                                                                                                                                                                                                                                                                                     |
| Safety parameters       | 
 
Patients with allergic rhinitis symptoms not adequately control are advised to walk-in to the ENT clinic without waiting for the appointment date.
 
                                                                                                                                                                                                                                                                                                                                                                                                                                                                                    |

|                            |                                                                                                                                                                                                                                                  |
|----------------------------|--------------------------------------------------------------------------------------------------------------------------------------------------------------------------------------------------------------------------------------------------|
|                            | 
 
Patients with allergic rhinitis co-exist asthma are advise to go emergency department if the asthma condition is uncontrolled.
 
                                                                 |
| Statistical methods | 
Sample size and power considerations
 
Control group: 70 participants
 
Intervention group: 70 participants
 
Consider 10% dropout rate, 77 participants are required from each group. 154 participants will be recruited.
 |

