The G-Power sample size calculator is used, and by setting the function of a repeated-measure ANOVA statistical test, the probability (power) at 0.8, the Type I error probability associated with this test of this null hypothesis at 0.05, and the effect size at 0.1885976, the sample size of 70 is calculated for each group as shown in the formulation of the calculation below.

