#### Sample size estimated using G-power calculator:

**F tests** - ANOVA: Repeated measures, between factors

**Analysis:** A priori: Compute required sample size

|                |                                   |             |
|----------------|-----------------------------------|-------------|
| Input:  | Effect size f                     | = 0.1885976 |
|                | $\alpha$ err prob                 | = 0.05      |
|                | Power (1- $\beta$ err prob)       | = 0.80      |
|                | Number of groups                  | = 2         |
|                | Number of measurements            | = 4         |
|                | Corr among rep measures           | = 0.5       |
| Output: | Noncentrality parameter $\lambda$ | = 7.9674683 |
|                | Critical F                        | = 3.9097293 |
|                | Numerator df                      | = 1.0000000 |
|                | Denominator df                    | = 138       |
|                | Total sample size                 | = 140       |
|                | Actual power                      | = 0.8003899 |

Therefore, a sample size of 70 are required for each group.

To estimate the sample size required to compare EQ-5D VAS between two groups, the input for the control group was derived from a study that evaluated general health-related quality of life among allergic rhinitis patients, where the mean and standard deviation score of EQ-5D VAS reported was  $72.1 \pm 19.0$  (Hoehle et al., 2017); whereas the input for the intervention group was derived from a study assessing QoL in the general Malaysian population with a reported mean and standard deviation of EQ-5D VAS at  $85.5 \pm 12.3$ , with

the rationale that the intervention group would achieve QoL similar to the general population (Shafie et al., 2019). By using the G power calculator and setting the function of a repeated-measures ANOVA statistical test, the probability (power), the Type I error probability associated with this test of the null hypothesis to 0.05, and the effect size to 0.3244754, the sample size of 25 is calculated for each group as shown in the formulation of the calculation below.

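### 77 per group covers about 9% dropout, not the stated 10%; at 10%, about 69 per group complete and EQ-5D-5L utility power is about 79.5%, not 80%

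*Combined protocol and SAP*

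**What the plan says.** The Sample size part of Section 5 reports six calculations and takes the largest. That is the EQ-5D-5L utility comparison, which closes with "Therefore, a sample size of 70 are required for each group" (total 140, actual power 0.8003899). Its targets are "the probability (power) at 0.8, the Type I error probability associated with this test of this null hypothesis at 0.05".

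The section then applies the dropout allowance: "By estimating the predicted drop-out rate of 10%, 77 participants for each group will be required for this phase". The Statistical methods row of the synopsis lists 70 per group and adds "Consider 10% dropout rate, 77 participants are required from each group. 154 participants will be recruited". Neither place writes out the inflation formula.

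Three other statements bear on the point:

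- Section 4 (Ethical conduct of the study) says that withdrawn participants are not replaced and that the data already collected from them go into the analysis.
- Statistical analysis specifies intention to treat, covering everyone randomised.
- The same section names two-way repeated-measures ANOVA in SPSS for every between-group comparison and gives no method for missing values.

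**The concern.** A dropout allowance should return the required number after the stated loss. Here 70 required, 10% lost and 77 recruited cannot all hold, because 10% of 77 is more than the 7 participants added.

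What is at stake is whether the stated 80% power is delivered at the dropout the plan itself predicts. The affected comparison is the one that fixed the size of the trial, and quality of life is one of the four primary endpoints in Table 1.

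**Working it through.** **Inputs for the utility calculation** (Section 5, Sample size)

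- Means and SDs: "values corresponding to moderate ( $0.909 \pm 0.095$ ) and mild ( $0.943 \pm 0.085$ ) were selected", with pooled SD 0.090139.
- Effect size and result: "the effect size at 0.1885976, the sample size of 70 is calculated for each group".
- "Number of measurements | = 4" and "Corr among rep measures | = 0.5"; two groups; alpha 0.05.

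**Step 1. Reproduce the plan's figure.**

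Effect size: f = (0.943 − 0.909)/(2 × 0.090139) = 0.1886, as entered.

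For the between-factor test in a repeated-measures ANOVA with total N, m measurements and correlation ρ:

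λ = f² × N × m / (1 + (m − 1)ρ), with 1 and N − 2 degrees of freedom.

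At N = 140: λ = 0.1885976² × 140 × 4 / (1 + 3 × 0.5) = 19.919/2.5 = 7.967. The critical F is 3.9097 and power is 0.8004. All three agree with the plan's output. N = 140 is the smallest even total that reaches 80%, so there is no slack.

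**Step 2. Check the dropout allowance.**

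- 70 × 1.10 = 77, the stated figure.
- 77 × 0.90 = 69.3 per group, or 154 × 0.90 = 138.6 in total.
- 1 − 70/77 = 7/77 = 9.1%, the largest dropout at which 77 still leaves 70.
- 70/0.90 = 77.8, which rounds up to 78; 78 × 0.90 = 70.2.

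**Step 3. Utility power at the numbers that remain** (same formula)

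| Total analysed | λ | Power |
|---|---|---|
| 140 | 7.967 | 0.8004 |
| 138.6 | 7.888 | 0.7964 |
| 138 (69 per group) | 7.854 | 0.7946 |

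The loss is 0.8004 − 0.7964 = 0.0040 at the expected number and 0.8004 − 0.7946 = 0.0058 at 69 per group.

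**Step 4. The other five calculations at 69 per group**, taking each effect size as the plan entered it

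| Calculation | Needed per group | Met at 69? |
|---|---|---|
| Within-group change | 69 | Yes (power 0.8057 at N = 138) |
| Knowledge | 67 | Yes (power 0.817 at N = 138) |
| EQ-5D VAS | 25 | Yes |
| TNSS | 18 | Yes |
| Adherence | 2 | Yes |

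Only the utility comparison falls below its target.

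**The case against.** **The analysis rules may remove the shortfall.** The plan says intention to treat and keeps the data of withdrawn participants. If all 154 contributed fully, the same formula would give power 0.837. This is the strongest reply, and it makes the finding conditional. It does not dispose of it. A standard repeated-measures ANOVA drops anyone with a missing visit, and the plan names no method that would keep partial records in. The allowance itself also treats dropouts as lost to the analysis; otherwise no inflation would be needed.

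**The gap is negligible.** It is one participant per group and about half a point of power. The assumed correlation matters more: at N = 140, a value of 0.45 or 0.55 in place of 0.5 gives power 0.824 or 0.777. The 10% is itself a prediction with no source given. All of this stands, and it limits the point to a correction of stated figures.

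**The multiplication is inferred.** No formula is printed. The exact match with 70 × 1.10 is suggestive only, but the inconsistency does not depend on how 77 was reached.

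**A stronger reading.** A reader might infer that the trial as a whole misses its sample-size requirement or is materially underpowered. The documents do not support that: five of the six calculations are met at 69 per group, and the sixth falls short by less than one percentage point.

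**Conclusion.** The point holds as a minor arithmetic inconsistency. The stated 77 per group protects the requirement of 70 up to about 9.1% dropout. At the stated 10%, about 69 per group remain, and power for EQ-5D-5L utility is about 79.5% against the stated 80%.

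This rests on two conditions: the plan's effect size and correlation are taken as given, and participants who drop out are lost to the repeated-measures ANOVA. The second follows from the named method when no missing-data approach is specified, but it sits uneasily with the intention-to-treat and withdrawn-data statements. If partial records were retained by a stated method, the loss would be smaller or absent.

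**What to change.** In the Statistical methods row of the synopsis and in the closing paragraph of the sample-size section, state that 77 per group (154 in total) allows for about 9% dropout, and that at 10% dropout about 69 per group complete and power for EQ-5D-5L utility is about 79.5%. This costs one sentence in each place and no extra patients.

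If the sponsor would rather keep both the 10% and the 80% as stated, the consistent figure is 78 per group, 156 in total. That adds two participants. The approximate total of 154 in the informed-consent section and the 77 per group assumed in the knowledge calculation would then need to be aligned.
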